## Exploratory Objective(s)

| **Exploratory Objective** | **Endpoint(s)** |
| --- | --- |
| 1. Longest duration of abstinence | 6 months |

# Study Design

## Characteristics

This is a phase I single site RCT of an extended contingency management intervention for smoking cessation for people experiencing homelessness and who are engaged in clinical care at the Tom Waddell Urban Health Clinic (TWUHC), Richard H. Fine People’s Clinic (RFPC), or the Positive Health Program (PHP) Clinic. Participants will be recruited from the TWUHC, RFPC, and PHP, and study procedures will take place at the Civic Center Plaza or at the Zuckerberg San Francisco General Hospital (ZSFG) courtyard to minimize risk from gathering in indoor locations during the COVID-19 pandemic. We will randomize 45 participants to the intervention arm and 45 participants to the control arm. Participants will receive usual cessation care at TWUHC, RFPC, or PHP, that includes weekly behavioral counseling and pharmacotherapy. The intervention will include the provision of financial incentives contingent on biochemically-verified abstinence for up to 6 months, with a potential to earn up to $620 in contingent reinforcements for cessation. Control group participants will receive $5 for attending each abstinence assessment. Participants will be asked to choose a quit date within 7 days of providing consent, and will meet study staff at TWUHC, RFPC, or PHP on the day of the quit attempt. Participants will meet daily for the first 7 days (week 1), twice weekly for the next 3 weeks (1 month), once weekly for the next 9 weeks (3 months), and monthly until the one-year follow-up (1 year). Assessment visit schedule is identical for both groups. At each of the scheduled assessment visits, participants will provide a CO sample and complete a short questionnaire on cigarette consumption, quit attempts since the last visit, the length of the last quit attempt, and use of medications and services. Questionnaires will be built on REDCap, and administered by study staff using an iPad. At enrollment, 2 weeks, 1 month, 3 months, 6 months, and 1-year follow-up, participants will be asked to complete structured questionnaires. The final study follow-up will be at 1 year.

## Sample Size

We expect to enroll 90 participants in the RCT, with 45 randomized to control and 45 randomized to intervention. We expect to screen 40 eligible participants per month, of which we anticipate that 10 (33% participation rate) will agree to enroll, for a goal enrollment of 8 participants per month over 12 months.

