# Abstract

| Title | Randomized trial of a contingency management smoking cessation intervention for homeless adults |
| --- | --- |
| Study Description | In this pilot randomized controlled trial (RCT), we will (1) adapt a known-efficacious extended CM cessation intervention to a novel population and setting, with the ultimate goal of increasing long-term abstinence among homeless adults seeking care in safety net health clinics, (2) develop a corresponding RCT protocol, and (3) conduct a pilot RCT to assess the feasibility and acceptability of the RCT. If the pilot RCT is feasible and acceptable, we will test the adapted intervention in a subsequently-funded, full-scale randomized controlled trial. |
| Study Intervention | In this study, we will test a contingency management intervention for carbon monoxide-verified smoking abstinence for people experiencing homelessness. |
| Study Population | The proposed study aims to enroll 90 homeless participants who are representative of the racial/ethnic and gender diversity of the homeless population in San Francisco. There are no exclusion criteria for this study based on gender, race, or ethnicity. We estimated our targeted enrollment based on the point-in-time count of the homeless population that occurred in 2010 in San Francisco. In 2019, there were 7499 unsheltered or publicly sheltered homeless persons in San Francisco, of whom 29% were white, 37% were black, 5% were American Indian/Alaskan Native, 5% were Asian, 2% were Native Hawaiian/Pacific Islander, 18% were Hispanic/Latino, 22% were mixed race, 35% were women, 4% identified as transgender, 1% as genderqueer/gender non-binary, and 1% as another gender. |
| Primary Objective | The primary objective is to assess feasibility and acceptability of:   - measuring biochemically-verified point prevalence abstinence at 6 months follow-up. - adhering to the protocol. - gathering information on the number of visits attended. - the retention protocol. |
| Secondary Objectives | - Assess feasibility and acceptability of measuring biochemically-verified 7-day point months follow-up at 3 months. - Assess feasibility and acceptability of measuring prolonged abstinence at 3 months and 6 months follow-up. - Assess feasibility and acceptability of measuring 12 point prevalence abstinence |
| Recruitment Methods | Recruitment methods include flyers, in-clinic recruitment, and via email to healthcare providers. |
| Sample Size | We plan to enroll 90 participants. |

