## Adherence Assessment

Using a combination of qualitative and quantitative methods, we will evaluate whether: 1) we met our screening and recruitment goals, 2) the randomization scheme worked and that participants were willing to be randomized, 3) the CM intervention was delivered with fidelity, 4) the retention procedures enabled tracking and retention, 5) the outcome assessments were valid, reliable, and complete, and 6) participants adhered to the protocol (Table 2).

| **Table 2: Feasibility and acceptability outcomes** | | |
| --- | --- | --- |
| Outcomes | **Measure** | **Threshold** |
| Screening | # opting out, # screened | 40 screened per month |
| Recruitment | # enrolled per month | 8/month for 12 months |
| Randomization | Proportion enrolled who are randomized | 90% randomized to intervention and control arms^32^ |
| Fidelity | Observations of incentive payment delivery | Incentive payments that are due are delivered within 2 days of the visit by study staff |
| Adherence | Protocol adherence to the CO assessment schedule  Attendance to counseling sessions  Adherence to NRT among those prescribed NRT | 75% of those enrolled will provide a CO sample at 60%-70%, i.e., 14 -17 out of 25 possible assessment visits^32,33^  75% will attend at least 6 out of 12 counseling sessions during the treatment duration^33^  75% will adhere to using NRT for at least half of the treatment duration^33^ |
| Retention | Proportion of the sample retained as a result of retention procedures | 2 weeks (85%), 3-month (85%), 6-month (75%), and 1 year (75%) retention rates |
| Assessment | Proportion who completed all questionnaires | 75% completed all questionnaires |
| Acceptability | Questionnaire and qualitative interviews with staff and patients | 75% satisfied with the overall intervention |

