### Accrual Estimates

We will recruit all participants by 1 year.

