## Statistical Analysis Plans

1. ***Statistical analyses****.* Because pilot studies are too small to definitively test hypotheses or estimate precise effect sizes, we do not propose any inferential statistics. Primary analyses will include descriptive statistics of the feasibility and acceptability indicators, comparing each statistic (e.g., % retained) to its tabled threshold (above, see Section 5.2). Above-threshold findings will suggest a reasonable level of feasibility and acceptability for the corresponding aspects of study procedures. Any sub-threshold finding would suggest that remedial modifications to study procedures and/or design would be required prior to moving forward with a full-scale RCT. We also will examine descriptive statistics of the primary and secondary clinical outcomes and include exploratory analyses of relevant biological variables such as age, sex, and race/ethnicity. To the extent possible, descriptive anaylses will consider whether feasibility and acceptability outcomes were consistent across service providers and service settings.

.

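### The recruitment threshold of 8 a month for 12 months totals 96 in a trial of 90, and, separately, 10 of 40 is labelled a 33% participation rate when it is 25%

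*Protocol*

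**What the plan says.** The planned number is given as a number enrolled. The Abstract states "We plan to enroll 90 participants", and Section 3.2 (Sample Size) states "We expect to enroll 90 participants in the RCT, with 45 randomized to control and 45 randomized to intervention".

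Section 3.2 then sets out the recruitment flow. It starts from "We expect to screen 40 eligible participants per month", and of these it anticipates that "10 (33% participation rate) will agree to enroll, for a goal enrollment of 8 participants per month over 12 months".

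Table 2, under Adherence Assessment, turns the goal into a feasibility criterion. The measure is the number enrolled per month and the threshold is "8/month for 12 months". The same table sets screening at 40 a month.

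Section 9.1.4 (Accrual Estimates) gives the accrual period: "We will recruit all participants by 1 year".

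Section 9.3 (Statistical Analysis Plans) compares each descriptive statistic with its tabled threshold and gives the consequence of falling short: "Any sub-threshold finding would suggest that remedial modifications to study procedures and/or design would be required" before a full-scale trial.

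**The concern.** This is a pilot whose primary aim is feasibility and acceptability, and it proposes no inferential statistics. The thresholds in Table 2 are therefore the standard against which its main results will be read. A threshold that disagrees with the planned sample size leaves the verdict on recruitment open to whichever reading is chosen, possibly after accrual has been seen.

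The participation rate is a different matter. It scores nothing in Table 2, but it is a stated planning assumption, and it does not follow from the two numbers printed beside it. A reader cannot tell what uptake the investigators expect.

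**Working it through.** **Inputs.** Enrolment 90 (Abstract; Section 3.2). Screened 40 a month (Section 3.2, where they are called eligible; Table 2). Agreeing to enrol 10 a month, labelled 33% (Section 3.2). Goal and threshold 8 a month for 12 months (Section 3.2; Table 2). Accrual complete by 1 year (Section 9.1.4).

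**Step 1: does the monthly goal give the planned enrolment?**

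- Rate × months = 8 × 12 = 96, not 90. The excess is 96 − 90 = 6, and 6/90 = 6.7%.
- The even monthly rate that gives 90 in 12 months is 90/12 = 7.5.
- The time to reach 90 at 8 a month is 90/8 = 11.25 months.
- The time to reach 90 at the anticipated 10 a month is 90/10 = 9 months.

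**Step 2: how would a completed enrolment of 90 be scored?**

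| Accrual pattern | Months open | As a 12-month total (needs 96) | As a rate while open (needs 8) |
| --- | --- | --- | --- |
| 90 spread evenly over the year | 12 | 90: below | 7.5: below |
| 8 a month until full | 11.25 | 90: below | 8: met |
| 10 a month until full | 9 | 90: below | 10: met |

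All three patterns meet the sample size and the accrual period. None meets the threshold read as a 12-month total, because enrolment stops at 90. The second and third pass or fail according to the reading. The first is below threshold on both readings, although it delivers the full sample on time.

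**Step 3: does the participation rate follow from its own figures?**

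- Agreeing/screened = 10/40 = 25%, against the stated 33%.
- For 33% of 40 the number agreeing would be 0.33 × 40 = 13.2, so about 13.
- For 10 to be 33%, the number screened would be 10/0.33 = 30.3, so about 30 (10/30 = 33.3%).
- The goal of 8 is 8/40 = 20%.

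On a base of 40, the figures 33%, 10 and 8 imply three different uptakes: 33%, 25% and 20%.

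**Step 4: are the two errors linked?** No. The goal of 8 a month is neither 33% of 40 (13.2) nor 25% of 40 (10). Correcting the percentage would leave the threshold as it is.

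**The case against.** The strongest reply is that the criterion works as a rate. Its measure is the number enrolled per month, and accrual is to finish by 1 year, not to be spread evenly across it. The stated goal is 8 a month with 10 anticipated. A trial that keeps to the goal fills in 11.25 months and meets the rate, the sample size and the accrual period together. The figure of 7.5 appears nowhere in the protocol. It may have been rounded up to 8, although the document does not say so. This stands in part. A reader might infer that any trial recruiting on plan must be scored below threshold, and the documents do not support that. But the rate reading sets aside the 12 months that the threshold itself names, and rounding would explain the mismatch without removing it.

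A second reply is that 96 might be enrolled so that 90 are randomized: 90/96 = 93.75%, above the 90% randomization threshold in Table 2. This does not stand, because the Abstract and Section 3.2 both give 90 as the number enrolled.

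Three further inferences are tempting and go too far:

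- That 33% lies behind the threshold. Step 4 shows that it does not.
- That a full-scale trial would screen too few people because of it. Nothing in the protocol says 33% will be carried forward, and the pilot will itself record screening, opting out and enrolment.
- That missing the threshold automatically triggers a redesign. Section 9.3 says only that a shortfall would suggest that modifications are required; it is not a formal stopping rule.

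**Conclusion.** Both errors are confirmed from the protocol's own figures.

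1. The recruitment threshold exceeds the planned enrolment by 6 participants (6.7%), or 0.5 a month against even accrual over the year. As a 12-month total it is unattainable; as a rate until 90 are enrolled it is attainable in 11.25 months. The text does not say which is meant, and the two give opposite verdicts on the same trial.
2. The participation rate is misstated: 10 of 40 is 25%, not 33%. This assumes that 40 and 10 are the intended entries. Table 2 repeats 40, which supports that figure, but the protocol does not show which of 40, 10 or 33% is wrong.

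Severity is minor to moderate. Recruitment is one of several descriptive benchmarks. The sample size was set on practical grounds, and no effect estimate, allocation or safety procedure is affected. It is still worth correcting, because the threshold is one that Section 9.3 applies directly.

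**What to change.** Before results are scored, restate the recruitment threshold in Table 2 so that it agrees with 90, and bring Section 3.2 into line. Either of two wordings would do:

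- 90 enrolled within 12 months (mean at least 7.5 a month). This fits the accrual statement in Section 9.1.4 but slightly loosens the criterion, from 8 to 7.5 a month, and the change should say so.
- At least 8 a month until 90 are enrolled (about 11.25 months). This keeps the monthly bar, but a trial that takes the full year would be scored below it.

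The choice is the investigators'. What matters is that it is made without reference to the accrual observed.

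Separately, reconcile 40, 10, 33% and 8 in Section 3.2 into one chain, and say how the goal of 8 relates to the 10 expected to agree. If 40 and 10 are correct, state 25%. If 33% is correct, change the count agreeing (about 13 of 40) or the base (10 of about 30), and in the latter case check it against the screening threshold in Table 2.

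The cost is a short amendment to the text. Design, procedures and sample size are unchanged. The stated participation rate will look less favourable if 25% is the right figure.

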## Primary Completion

The expected primary completion date is 18 months after the study opens to accrual.

## Study Completion

The expected study completion date is 2 years after the study opens to accrual.

# Selection and Enrollment of Participants

## Eligibility Criteria

### Inclusion Criteria

In order to be eligible to participate in this study, an individual must meet all of the following criteria:

1. Are 18 years or older,
2. Attend an in-person visit at the Tom Waddell Urban Health Clinic, Richard H. Fine People’s Clinic, or the Positive Health Program Clinic,
3. Meet criteria for homelessness as defined by the Homeless Emergency Assistance and Rapid Transition to Housing Act,
4. Are current smokers (smoked at least 100 cigarettes in lifetime, smoked daily in the past 7 days and at least 5 cigarettes per day, verified by expired Carbon Monoxide (CO)≥ 8 parts per million (ppm)),
5. Have an intention to quit smoking within the next six months,
6. Are attending on-site smoking cessation counseling provided by the behavioral counselors,
7. Are English proficient, and
8. Are able to provide informed consent. Patients who are interested in participating but not enrolled in counseling services will be given the opportunity to join weekly one-on-one counseling for a period of 2 weeks prior to enrollment.

### Exclusion Criteria

An individual who meets any of the following criteria will be excluded from participation in this study:

1. Are unable to take nicotine replacement therapy (e.g., pregnancy or MI within the past 2 weeks)

## Recruitment Methods

The study recruitment strategy aims to achieve representation of minority groups that reflects the demographics of the affected population in the catchment area. HIPAA-trained study staff will be present during scheduled clinic sessions to recruit patients. Prior to each clinic session, study staff will use the EHR to identify smoking patients among those scheduled to be seen. Study staff will approach patients who have screened positive for cigarette smoking during intake prior to their primary care or urgent care visits, confirm cigarette smoking status, ask whether they would be interested in hearing about a research study, and screen for basic study eligibility. Study staff will also recruit participants using flyers in the clinic waiting area, and have interested participants call study staff at the designated phone numbers. Lastly, study staff will email providers at the clinic to inform them about the study and ask them to either refer interested patients and request permission to contact potentially eligible patients for the study via telephone.

Participants from the TWUHC, RFPC, and PHP, who meet study criteria will complete enrollment procedures at the time of eligibility or within 1 week of recruitment either by telephone or in person at the Civic Center Plaza or the Zuckerberg San Francisco General Hospital courtyard, the primary study site for the study. Study activities will also take place at the RFPC and PHP, both located at the ZSFG. Study staff will describe study procedures and obtain written informed consent using the teach-to-goal method at the time of eligibility. We will conduct all in person procedures at the Civic Center Plaza or at ZSFG.

The study site has been modified from the TWUHC to the Civic Center Plaza and the courtyard outside of ZSFG because the clinics have reduced their capacity for in-person evaluation because of the COVID19 pandemic. To minimize risk of transmission, we have identified the Civic Center Plaza, an outdoor site, as an alternative study site for the study. We will follow the San Francisco Department of Public Health guidance for preventing transmission of viruses. All participants will be provided a mask if they don’t have one. We will pick a quiet spot at the plaza, and meet participants one at a time to maintain privacy and confidentiality.

## Inclusion of Women and Minorities

### Eligibility of Women and Minorities

Individuals of any sex/gender, race, or ethnicity are eligible for this study. There are no exclusion criteria for this study based on gender, race, or ethnicity. We estimated our targeted enrollment based on the point-in-time count of the homeless population that occurred in 2010 in San Francisco (See Targeted Enrollment Table). In 2019, there were 7499 unsheltered or publicly sheltered homeless persons in San Francisco, of whom 29% were white, 37% were black, 5% were American Indian/Alaskan Native, 5% were Asian, 2% were Native Hawaiian/Pacific Islander, 18% were Hispanic/Latino, 22% were mixed race, 35% were women, 4% identified as transgender, 1% as genderqueer/gender non-binary, and 1% as another gender.

### Recruitment of Women and Minorities

The study recruitment strategy aims to achieve representation of minority groups that reflects the demographics of the affected population in the catchment area.

## Inclusion Across the Lifespan

### Age Range of Participants

Individuals ages 18 and over are eligible for this study. No children under the age of 18 years of age will be included in this study of adult cigarette smokers. Eligible participants will include those who are ≥ 18 years of age. The tobacco use profile and the likely response to interventions among homeless youth smokers is sufficiently different from that of homeless adult smokers, warranting separate studies of homeless youth and adult cigarette smokers. Moreover, the proposed CM intervention is based on prior studies of adults and not youth participants.

### Study Design/Recruitment Considerations Related to Age Groups

The study design and recruitment strategy aim to achieve representation of age groups that reflect the demographics of the affected population. We will recruit participants that reflect the age and gender diversity of people experiencing homelessness in San Francisco (See eligibility criteria and inclusion of women and minorities sections above).

## Participant Registration

A written, signed, informed consent form (ICF) and a Health Insurance Portability and Accountability Act (HIPAA) authorization must be obtained before any study-specific assessments are initiated. A copy of the signed ICF will be given to the subject and a copy will be filed in the medical record. The original will be kept on file with the study records.

All participants consented to the study will be registered in OnCore®, the UCSF Helen Diller Family Comprehensive Cancer Center Clinical Trial Management System (CTMS). The system is password protected and meets HIPAA requirements.

## Randomization/Assignment to Intervention

Randomization will be stratified by recruiter and a binary nicotine dependency code determined by participant response to a single item asked during study enrollment: "How soon after you wake up do you smoke your first cigarette?" (≤30 minutes coded as 'high' dependency; >30 minutes coded as 'low' dependency; Fagerström 2003). Before initiating the study, stratum-specific sequential ID numbers will be randomly pre-assigned to experimental groups in blocks of random size. The PI will be blinded to this assignment, and only the study’s statistician ([name]) will have access to the linkage between ID numbers and intervention assignments. The study ID numbers and corresponding experimental group assignments will be preloaded into REDCap. When a participant is enrolled, REDCap will assign the first available ID number within the appropriate stratum. After completing the baseline interview, participants will be informed of their study ID number and their experimental group assignment. The study will randomize 45 participants to the intervention arm and 45 to the control arm (n=90).

## Blinding

In the proposed Feasibility and Acceptability RCT and the subsequent RCT, the PI will stay blinded and study staff will be responsible for the incentive payments, collecting the study data, and this information will not be shared with the PI. Any progress report prepared during the study will not reveal intervention assignments, and the study’s statistician will not share any unblinded results with the PI. We have clarified this in the protocol.

